#### Patient withdrawal

In consenting to the trial, patients are consenting to the trial treatment, follow-up and data collection. If withdrawal of the randomly allocated treatment occurs, patients should still be followed up where they agree. Patients are allowed to withdraw without giving reason at any time and a withdrawal case report form (CRF) will be completed to document the date and reason (where given) for withdrawal. Data collected up to the time of withdrawal will be included in analyses. Health professionals will assess patients’ capacity to take part in the rehabilitation programme and the study; if they have been deemed to have lost capacity to consent they will be withdrawn from the study but the data already collected will be retained.

### Interviews with patients

All participants are offered an interview (even those who withdraw from the trial) in their own home after the final follow-up to assess their experiences of the intervention and trial processes. Family members/carers may also attend the interview at the participants’ request.

### Focus groups with health professionals

Health professionals from Trafford and Manchester City who are involved in the study are recruited to participate in a focus group at the end of the study (after 24-week follow-up). All members of staff (n=8) will be given study information by their team leader and asked if they are available for a focus group; the focus groups will take part at their place of work at a time convenient to each team. Participating staff can choose to be part of a one-to-one interview if they prefer not to be interviewed with colleagues or if for staffing reasons it is not feasible for them to attend the focus group.

### The intervention

Full details of the intervention components are shown in online supplementary material: table 1 (Template for Intervention Description and Replication (TIDieR) Guidelines).

10.1136/bmjopen-2018-028100.supp3Supplementary data

#### The technology

The Samsung Galaxy J5 as a means of communication^27^ will be provided to all participants and health professionals. Samsung phones have been used previously in our research, with good usability and have the correct specification for the falls detector to work.^10^ The research team will provide technical support for participants and health professionals ([name]) and any required application updates ([name]).

##### ‘Motivate me’ app

The ‘Motivate me’ app is the health professional application. This app is used by the health professional with the patient to set behavioural/outcome-based goals, for the health professional to see what exercises the patient has reported and to give feedback and to check they have received messages (online supplementary figure 1).

10.1136/bmjopen-2018-028100.supp1Supplementary data

##### ‘My activity programme’

‘My activity programme’ is the patients application. This app will be used by the patient to report the exercises they have done, receive messages and prompts and to confirm whether they like the messages received (online supplementary figure 2).

10.1136/bmjopen-2018-028100.supp2Supplementary data

There are 12-behaviour change techniques adopted^28^ through the intervention include goal setting (behaviour/outcome), action planning (recording plan to exercise in diary on smartphone/reminder text messages when it is time to start the programme) and feedback on behaviour (providing feedback on what they have done/benefits). The key behavioural change techniques delivered as part of the control and intervention arms are outlined in table 2.

**Table 2 T2:** Behaviour change techniques adopted*

	1. Intervention arm	1a How	2. Control arm (standard service)	2a How
1.1 Goal setting (behaviour)	x	What, when, where—smartphone and paper	x	What, Where—paper
1.3 Goal setting (outcome)	x	Smartphone verbally	x	Verbally
1.4 Action planning	x	Smartphone		
1.5 Review behavioural goals	x	Smartphone verbally	x	Paper verbally
1.7 Review outcome goals	x	Smartphone verbally	x	Verbally
2.2 Feedback on behaviour	x	Smartphone verbally	x	Verbally
4.1 Instructions on how to perform the behaviour	x	Physically smartphone paper	x	Physically Paper
5.1 Information about health consequences	x	Smartphone verbally (ad hoc)	x	Verbally (ad hoc)
5.6 Emotional consequences	x	Smartphones verbally (ad hoc)	x	Verbally (ad hoc)
6.1 Demonstration of behaviour	x	Physically	x	Physically
7.1 Prompts	x	Smartphone		
8.7 Graded tasks	x	Smartphone paper	x	Paper

*Based on Michie *et al’s*
28 behaviour change taxonomy.

### The control

Standard service is variable across different sites, but all sites deliver a mix of the evidence-based Falls Management Programme and Otago^29^ exercises as standard care.

They include face-to-face delivery once-a-week and a prescribed home-exercise programme (with booklet) with informal outcome-based goal setting.

Manchester City: Once a week visits (either home-based or group exercise) for around 12 weeks (dependent on need) and then check-ups until 6 months discharge.

Trafford: 8-week group exercise once a week then discharged, or 6-week home-based exercise then discharged or referred to further 8-week group exercise.

Both sites leave participants with a home exercise plan on discharge and where appropriate refer onto community-based strength and balance programmes.

#### Control application for self-reporting exercise

The control arm receives a study phone with a basic app where they report their exercises, but they are only able to report their exercises (outcome measure), they are not able to view their programme, receive messages or receive feedback on the phone. The health professional is not able to view what they have reported (outcome measure for the research team only), thereby minimising risk of contamination.

### Co-Treatments

Trial participants are free to seek management of falls and other related or unrelated medical conditions during the course of the trial. We record all health service resource use and these will be reported as a trial outcome. At trial closure, participants will continue with usual healthcare; no further ancillary care is provided beyond that immediately required for the proper and safe conduct of the trial.

### Outcome measures

Data such as demographics (age, gender, socio-economics, health conditions, falls history, previous smartphone/mobile phone use and wifi) and physical tests are recorded on the CRF (table 3).

**Table 3 T3:** Schedule of enrolment interventions and assessments

	Study period					
	Enrolment	Allocation	Post-allocation			Post-intervention
Timepoint	−***t_1_***	**0**	***T_1_***	***T_2_***	***T_3_***	
Enrolment						
Eligibility screen	X					
Consent to further information	X					
Tech demo and Informed consent	X					
Allocation		X				
Interventions:						
*Control:* *Manchester City* ***Trafford***			 			
*Intervention*						
Assessments:						
Gender Age Ethnicity Education Housing Falls history Medical history Previous mobile/smartphone use Allocated to home or group exercise	X					
*Falls (calendar*) *Falls (alarm*) *My activity self-report* *Prescribed exercise plan* ***Face-to-face delivery***						
*Berg* *TUG mTUG* *30 s Chair stand* *FES-1* *EQ5D* *Resource use* ***Health professional time resource*** *ICE-CAP-O* ***EARS***	X			X	X	
*Interviews* ***Focus groups***						X

EARS, Exercise Adherence Rating Scale; EQ5D, EuroQol five dimension scale; FES, Falls Efficacy Scale; ICE-CAP-O, ICEpop CAPability measure for Older people; mTUG, Mobile based instrumented Timed up and go test; TUG, Timed up and go test.

#### Primary outcome measures

Assess feasibility and acceptability of the design and procedures including:

Willingness of participants to be randomised (collected on the screening section of the CRF/interviews).Willingness of clinicians to recruit participants (through focus group/completion of screening on the CRF).Number of eligible patients (through the CRF and documentation of number of monthly referrals to falls services).Whether demonstration by peer of the technology aids recruitment.Characteristics of the proposed outcome measures, for example reliability of falls detector when compared with falls calendars, whether a self-report app is a reliable outcome measure.Follow-up rates, adherence/compliance rates.Time needed to collect and analyse data.Determine effect sizes for use in sample-size calculations, enabling power calculations for the reduction in falls for a definitive large-scale RCT.

Start/stop criteria for going to full trial are included in Consolidated Standards of Reporting Trials (CONSORT) diagram (diagram 1) based on these outcome measures.

We will also report intervention fidelity, process and compliance using observation during quality assurance visits. Health professionals and the assessors will follow a standard operating procedure for assessment and intervention. The trial treatment record (CRF) includes details of the grade and type of staff involved with delivery. The health professionals and researcher will keep an issue log of technical issues with the phones or apps during the trial either experienced directly or reported by participants. We will also explore the potential impact of differing length of exercise delivery across sites.

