#### Recruitment, consent, sample size

Health professionals give patients the study information sheet and inform them about the intervention. The health professionals then ask the patient if they are happy to be contacted by the researcher who demonstrates the technology either in the patient’s home or within groups at each NHS site. The technology is demonstrated to the participant before they are asked to give informed consent. Where possible a former patient who has used the smartphone applications accompanies the researcher to demonstrate the technology. We think involvement of a peer has the potential to assist in promoting patient confidence in the use of the technology.

The first 36 eligible patients identified through each service (n=72 in total) who are willing to participate are being recruited and randomised (figure 1). Thirty patients per arm after attrition (approx. 10%) are normally used for feasibility RCTs.^26^ Study participants are randomised using a computer-generated randomisation algorithm at sealedenvelope.com, stratified by gender and site, using block randomisation (2, 4, 6 blocks) into either intervention or control group. Stratification is by gender and site to ensure equal distribution across sites as we are testing all trial procedures.

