#### Outcome measures

##### Falls

The primary outcome for any future definitive trial would be falls, expressed as fall rate per person per months of follow-up observation after randomisation. This study collects falls data for the purposes of testing feasibility of data collection, and to inform us of falls rates and intervention effect size for a future sample size calculation.

All participants will wear the smartphone in their pocket or on a waistband and this will act as a falls detector, running the FallsMonitor@home app developed by the University of Bologna.^10^ If the patient chooses then they can also use the app on the phone as a falls alarm. The fall detection system application allows the user to identify a list of formal/informal caregivers who will receive an SMS if a fall is detected. Patients are given an opportunity to de-active the falls alarm through an application on the smartphone if there is a false alarm, enabling the user to maintain control and prevent unwanted intrusion. Participants are asked if we can use their anonymised falls data for further development of the app and in the FARSEEING real-world falls database.^30^

To validate this as an outcome measure we use the internationally agreed Prevention of Falls Network Europe (ProFaNE) falls definition^31^ and follow the agreed ProFaNE falls data collection and analysis protocols based on self-report calendars.^32^

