##### Balance

The Berg Balance Scale will be used to assess balance. This has good validity and sensitivity in this population^34^ and is one of the best outcome measures for assessing standing balance.^35^ It has also been used for the prediction of falls.^36^ The effect sizes from this outcome measure scale will be used as part of the power calculation for the full trial.

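### The fall-rate effect observed in about 30 patients per arm is too imprecise to feed the definitive trial's sample size, and the role of the Berg effect size in that calculation is not explained

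*Protocol article*

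**What the plan says.** Under Primary outcome measures, the last item in the list of feasibility outcomes is: "Determine effect sizes for use in sample-size calculations, enabling power calculations for the reduction in falls for a definitive large-scale RCT". Under Falls, the data are collected partly "to inform us of falls rates and intervention effect size for a future sample size calculation". The same section fixes the later trial's endpoint: "The primary outcome for any future definitive trial would be falls, expressed as fall rate per person per months of follow-up observation after randomisation". Under Balance, the article says of the Berg scale: "The effect sizes from this outcome measure scale will be used as part of the power calculation for the full trial".

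On size, under Recruitment, consent, sample size: "The first 36 eligible patients identified through each service (n=72 in total) who are willing to participate are being recruited and randomised", with the reason that "Thirty patients per arm after attrition (approx. 10%) are normally used for feasibility RCTs". Allocation is by blocks of 2, 4 and 6 into two arms, which I take as 1:1. Follow-up ends at six months. The Analysis section promises a mainly descriptive analysis with means, SDs and 95% CIs for between-group differences, and a statistical analysis plan that is not shown here. Nothing in the article says that the definitive trial's target effect will be set independently of the effect observed in this one.

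**The concern.** A sample size needs two kinds of input: a target difference, and nuisance parameters such as the event rate, dispersion or SD. A feasibility trial can reasonably inform the second kind. It informs the first kind poorly, because the required size varies roughly with the inverse square of the log rate ratio, so error in the estimate is magnified. A ratio that looks favourable by chance leads to an underpowered definitive trial, and a ratio of 1 or above gives no sample size for a reduction at all.

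The Berg sentence raises a separate question. A difference on a balance scale is not an input to a power calculation for a fall rate, and the article does not say how the two are connected.

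**Working it through.** **The plan's own figure.** Thirty per arm after 10% attrition needs 30/0.9 = 33.3, so 34 per arm or 68 in total. The planned 72 retains 72 × 0.9 = 64.8, about 32 per arm. It is slightly generous and is not at fault. I use 30 to 32 evaluable per arm.

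**Assumptions for falls (none is in the document).** True rate ratio RR = 0.77; control mean μ = 0.5 to 1.0 falls per person over six months; negative-binomial dispersion k = 0.5 to 1.5.

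**Precision.** SE(log RR) = √[(1/μ + 1/(μ·RR) + 2k)/n].

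| n per arm | μ | k | SE(log RR) | Typical 95% CI | P(observed RR ≥ 1) | P(observed RR < 0.60) |
|---|---|---|---|---|---|---|
| 32 | 1.0 | 0.5 | √[(1 + 1.299 + 1)/32] = 0.32 | 0.41 to 1.44 | 21% | 22% |
| 32 | 0.5 | 1.5 | √[(2 + 2.597 + 3)/32] = 0.49 | 0.30 to 2.00 | 30% | 30% |
| 30 | 1.0 | 0.5 | 0.33 | 0.40 to 1.48 | 21% | 23% |
| 30 | 0.5 | 1.5 | 0.50 | 0.29 to 2.07 | 30% | 31% |

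The CI is exp(ln 0.77 ± 1.96·SE). The probabilities are the normal tail areas at 0.261/SE and 0.249/SE, since ln 0.77 = −0.261 and ln 0.60 − ln 0.77 = −0.249.

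**Effect on the definitive trial.** Assume 1 control fall per person over its follow-up, k = 1, two-sided 5% and 90% power: N per arm = (1.96 + 1.282)² × (1/μ + 1/(μ·RR) + 2k)/(ln RR)².

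- Planning at RR = 0.60: 10.51 × 4.667/0.2609 ≈ 188.
- Planning at RR = 0.70: 10.51 × 4.429/0.1272 ≈ 366.
- Planning at RR = 0.77: 10.51 × 4.299/0.0683 ≈ 661.

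With 188 per arm and a true ratio of 0.77, SE = √(4.299/188) = 0.151 and power = Φ(0.261/0.151 − 1.96) ≈ 41%.

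**Sensitivity.**

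- *Other inputs.* With a true ratio of 0.75, 30 per arm, 0.5 to 3 falls per person-year and k of 0.5 to 2, the narrowest CI is 0.42 to 1.33 and the widest 0.20 to 2.77. All include 1.
- *Simulation.* In 20,000 simulated feasibility trials at each of 1 and 2 falls per person-year (k = 1, true ratio 0.75), 24% to 31% observed a ratio of 1 or more. Of the rest, 65% to 71% led to a 12-month definitive trial, planned for 80% power, whose true power was below 80%.
- *A favourable case.* Even at 3 falls per person in six months and k = 0.25, with 32 per arm and a true ratio of 0.77, the CI is 0.52 to 1.14.

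**Berg.** With 30 per arm and an observed standardised difference of 0.3, SE = √(2/30 + 0.09/120) = 0.26 and the 95% CI is −0.21 to 0.81. At 80% power the implied size is 175 per arm at 0.3, 24 at 0.81, and undefined at or below 0.

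**Nuisance parameters by contrast.** A pooled SD on 58 degrees of freedom has a 95% CI of 0.85 to 1.22 times its estimate, so N for a fixed target difference moves by 0.72 to 1.49 times. The control fall rate is less secure: SE(log rate) = √[(1/μ + k)/n] is 0.22 to 0.34, a 95% CI factor of about 1.5 to 2.0 either way. Both are imprecise, but both always give a finite, usable answer.

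**The case against.** The strongest reply is that the text is softer than it first looks. Falls data are to inform a later calculation, Berg effects are only part of it, and the promised 95% CIs would expose the imprecision. A later trial would have its own protocol and review, and nothing here touches this trial's participants, randomisation or descriptive analysis. All of that stands, and it limits the severity. It does not remove the stated use of the observed effect in the sample-size calculation, since no independent target is mentioned.

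Four stronger readings are tempting but not supported:

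- *The observed effect will be the sole input.* The wording leaves room for others.
- *The fall rate is not a planned output.* The Falls section names falls rates expressly, and the choice of count model and dispersion may sit in the analysis plan not shown.
- *A Berg effect will be put into a fall-rate formula.* The Balance section does not say so. It may mean power for a secondary outcome, and Berg is listed among the key secondary outcomes here. What is established is an unexplained link.
- *A chance-null estimate would stop the programme.* The start/stop criteria are in a figure that is not shown. They are said to be based on the listed outcomes, but whether any threshold concerns the effect is unknown.

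It is also fair that the numbers rest on assumed inputs. Both arms receive exercise rehabilitation, so the added effect of the app may differ from 0.77. An effect closer to 1 would be harder still to distinguish from none at this size.

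**Conclusion.** The point holds for the planned use of the observed fall-rate effect. Under the assumed inputs, between about one in five and one in three feasibility trials of this size would observe no reduction although a true one exists. A similar share would observe a ratio below 0.60, which would plan the definitive trial at less than a third of the size needed (188 against 661 per arm). The exact figures depend on the assumed rate, dispersion and true ratio; the conclusion held in every scenario tried. For Berg, the finding is that the Balance and Falls sections must be reconciled, not that an error is proven. The sample size of 72 is not in question. This should be fixed, but it does not threaten the conduct or validity of the feasibility trial itself.

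**What to change.** In Primary outcome measures and in Falls, state that the definitive trial will be powered for a worthwhile reduction in fall rate agreed in advance. Take from this trial the control-arm fall rate, its dispersion, outcome SDs and retention, and allow for their uncertainty, for example by carrying the cautious confidence limit into the calculation. Report the observed between-arm effect with its 95% CI as description only. In Balance, either remove Berg from the falls power calculation or say that it serves a power check for a secondary outcome and that its SD is what will be used.

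The cost is wording in the protocol and analysis plan and one count model on data already being collected. No extra patients or visits are needed.

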#### Outcome measures

##### Falls

The primary outcome for any future definitive trial would be falls, expressed as fall rate per person per months of follow-up observation after randomisation. This study collects falls data for the purposes of testing feasibility of data collection, and to inform us of falls rates and intervention effect size for a future sample size calculation.

All participants will wear the smartphone in their pocket or on a waistband and this will act as a falls detector, running the FallsMonitor@home app developed by the University of Bologna.^10^ If the patient chooses then they can also use the app on the phone as a falls alarm. The fall detection system application allows the user to identify a list of formal/informal caregivers who will receive an SMS if a fall is detected. Patients are given an opportunity to de-active the falls alarm through an application on the smartphone if there is a false alarm, enabling the user to maintain control and prevent unwanted intrusion. Participants are asked if we can use their anonymised falls data for further development of the app and in the FARSEEING real-world falls database.^30^

To validate this as an outcome measure we use the internationally agreed Prevention of Falls Network Europe (ProFaNE) falls definition^31^ and follow the agreed ProFaNE falls data collection and analysis protocols based on self-report calendars.^32^

##### Fear of falling

Short Falls Efficacy Scale-International (Short FES-I) is used to measure fear of falling.^33^ This is often a measure used by UK falls services as part of standard outcome measures.

##### Function

The TUG will be used to assess improvements in mobility and function. The TUG will be applied as described by Podsiadlo and Richardson.^25^ Participants will be asked to perform the TUG at their self-selected habitual walking speed. A medical device implementing an instrumented version of the TUG will be used (mTUG, mHealth Technologies). The device is able to automatically provide guidance to the user for administering the test, capture and process the data, and generate summary reports of function for the health professional. The blinded assessor will complete the normal TUG and the mTUG as outcome measures (the standard TUG as a validation measure) to explore whether the mTUG is usable as an outcome measurement for the definitive RCT. The health professional will carry out the mTUG with a sub-sample of 10 patients at each site to assess their experiences of its use.

##### Balance

The Berg Balance Scale will be used to assess balance. This has good validity and sensitivity in this population^34^ and is one of the best outcome measures for assessing standing balance.^35^ It has also been used for the prediction of falls.^36^ The effect sizes from this outcome measure scale will be used as part of the power calculation for the full trial.

##### Strength

30 s Chair stand test,^37^ which has good validity and is used throughout health services, will be used to assess physical ability, in particular strength.

